# Efficacy of self-management exercise program with spa therapy for behavioral management of knee osteoarthritis: research protocol for a quasi-randomized controlled trial (GEET one)

**DOI:** 10.1186/s12906-018-2339-x

**Published:** 2018-10-16

**Keywords:** Knee osteoarthritis, Exercise, Self-management, Education, Spa therapy

## Abstract

**Background:**

Osteoarthritis (OA) is not limited to joint pain and stiffness, which can lead to disability; it is also linked to comorbidities such as overweight, obesity and fears and beliefs related to the pathology. The knee OA population appears more affected by these risk factors and has a lower physical activity (PA) level than the general population. The key challenge for OA treatment is increasing the PA level to decrease the risk factors.

**Methods:**

We aim to perform a prospective, multicentric, quasi-randomized controlled trial with an alternate-month design (1-month periods). People aged 50–75 years old with symptomatic knee OA (stage I-IV Kellgren and Lawrence scale) with low and moderate PA level will be included in 3 spa therapy resorts. The experimental arm will receive 5 self-management exercise sessions (1.5 h each; education, aerobics, strength training, range of motion) + an information booklet + 18 sessions (1 h each) of spa therapy treatment (STT). The active comparator arm will receive an information booklet + 18 sessions of STT. The primary outcome will be a change at 3 months in PA level (International Physical Activity Questionnaire short form score). Secondary outcomes will be function (WOMAC) pain (numerical scale), anxiety/depression (HAD), fears and beliefs about OA (KOFBeQ) and arthritis self-efficacy (ASES). The barriers to and facilitators of regular PA practice will be assessed by using specific items specifically designed for the study because of lack of any reference scale.

**Discussion:**

The study could demonstrate the impact of a self-management exercise program associated with spa therapy in the medium term by increasing PA level in people with OA. A benefit for ameliorating fears and beliefs and anxiety/depression and improving self-efficacy will also be analysed. The findings could offer new prospects while establishing best clinical practice guidelines for this population.

**Trial registration:**

ClinicalTrials.gov NCT02598804 (November 5, 2015).

**Electronic supplementary material:**

The online version of this article (10.1186/s12906-018-2339-x) contains supplementary material, which is available to authorized users.

## Background

Osteoarthritis (OA) constitutes the most frequent chronic joint disease. It contributes widely to disability and loss of autonomy in older people [1]. OA localization at the knee, hip and hand are most at risk [2]. According to the World Health Organisation (WHO), in 2020, chronic disease will be the main source of disability. This evolution is related to the increase in life expectancy due to improvements in medical technology [3].

Risk factors are multiple: heredity, overweight and trauma (sports, professional, surgery) [4, 5]. All these factors interact with each other and may contribute to worsened pain and disability and reduced mobility. With lack of any curative treatment, except prosthetic surgery, non-pharmacological treatment is essential [6].

International guidelines such as from the Osteoarthritis Research Society International (OARSI) recommend a non-pharmacological intervention associated with pharmacological treatment for pain for people with knee OA. Non-pharmacological therapies are exercise programs (strength training, aerobic activity, adjunctive range of motion, stretching and increasing physical activity (PA) level), self-management education program and weight loss if necessary [7–9]. Education and self-management exercise have a positive impact on pain, function, exercise level, weight, quality of life, and treatment adherence [10]. Self-management exercise programs have a clinical and behavioral impact [11].

People with OA have less PA level than the general population [12]. Comorbidities and risk of death are increased: history of diabetes, cancer, or cardiovascular disease and the presence of waling disability are major risk factors. People with more concerns are less active. PA practice can have two effects: ameliorating comorbidities and alleviating knee OA symptoms. However, adherence to non-pharmacological treatment is often incomplete. To be fully effective, an exercise program must be accompanied by measures to promote therapeutic adherence. Among these measures, education and information improve guideline adherence [11].

The efficacy of spa therapy in OA has been demonstrated, with good level of evidence for pain and disability, but the effect on behavioral management such as PA level is still unknown [13]. The last OARSI recommendation include spa therapy but restricted spa treatment to a subgroup of patients with generalized OA with comorbidities because of a lack of evidence [7]. Spa therapy effect is well known on pain, physical function [14, 15] and symptomatic drug consumption [16]. Short and long-term efficacy (up to 9 months) were demonstrated [16] on painful symptomatology and functional capacities in knee osteoarthritis people. Average direct costs per patient were higher in the usual treatment than mud-bath therapy in addition to usual care [17]. Mechanisms of action in spa therapy treatment are not fully understood but a combination of factors: mechanical, thermal and chemical seems to be the most evident [18]. Recent research on possible biomarkers showed a significant increase of Carboxy Terminal cross-linked Telepeptides of Type II (CTX-II), two weeks after mud-bath therapy [19]. According to Giannitti [20], mud-bath therapy decrease whole-blood level of miR-155, miR-181a, miR-146a, and miR-223 expression levels for knee osteoarthritis people. Furthermore mud-bath therapy modifies an important mediators of cartilage metabolism, the plasma levels of the adiponectin [21].

SPA therapy resorts, common in Europe, include a large sample of patients with different phenotypes from early to advanced OA stages. The spa treatment context could offer good conditions for behavioral modification and could be a special opportunity for self-management education. The spa resort is the opportunity to meet and interact with other patients and benefit from multidisciplinary medical and paramedical support for ameliorating pain and disability [22]. A combination of spa therapy, physical exercise, and self-management was found to benefit fibromyalgia symptoms [23]. Another study of low back pain, self-management exercise and spa therapy treatment (STT) is under way [24].

We aim to conduct a multicentre, prospective, quasi-randomised study to evaluate the effectiveness of a self-management exercise program associated with STT versus STT alone, on the physical activity level of patient with knee osteoarthritis, at 3 months follow up.

## Methods

### Aim

This study is aimed at people with knee OA. The main objective is to show a change in PA level 3 months after the self-management education program associated with STT. Secondary objectives are to assess the effectiveness of the self-management exercise program in terms of pain, disability, anxiety, depression, self-efficacy, fears and beliefs and barriers to and facilitators of OA and PA at 3 months, and sarcopenia after treatment (18 days).

### Study design and setting

This is a 2-year multicenter, prospective, comparative, and quasi-randomized trial. The population will be randomised according to the alternate-month design method in 2 arms: experimental and active comparator.

The design and conduct of this trial will adhere to the requirements of the Standard Protocol Items: Recommendations for Interventional Trials (SPIRIT) [25]**.** The results will be reported in accordance with the CONSORT Statement for non-pharmacologic trials [26].

### Participants and recruitment

We will recruit 142 participants, male and female, who are 50–75 years old with a diagnosis of mono or bilateral knee OA, in 3 spa therapy resorts, in France. All people already registered for STT will receive an information letter with study notification and eligibility criteria. Posters in each participating spa resort will be used for recruitment. The center is Clermont-Ferrand University Hospital associated with Royat spa center, le Mont Dore spa center and Bourbon-Lancy spa center.

Patient recruitment potential among people with knee OA in spa therapy is important. Indeed, OA represents the main disease treated by spa therapy (250,000 per year in France).

For people who meet the inclusion criteria, the research coordinator will perform the information and consent process and the physician will verify the inclusion criteria.

### Eligibility criteria

#### Inclusion criteria

People, male or female, 50 to 75 years oldMono or bilateral knee OA according to American College of Rheumatology (ACR) criteria [27]Radiological score: stage I to IV on Kellgren and Lawrence scaleCovered under the national health insuranceGiving informed written consent to participate in the study

#### Exclusion criteria

Contraindication to spa therapyUnstable anginaCardiac failureBehavioral disorders or comprehension difficulties making assessment impossibleHigh PA level according to International Physical Activity Questionnaire (IPAQ) categorical score [28]

### Randomisation

The population was randomized according to the alternate month design method in two arms: experimental and active comparative arm. Weingarten, highlight that’s it’s possible to avoid contamination between the 2 groups with a therapeutic window between the intervention period and control period [29]. This methodology was previously used with good level of evidence in a self-management education program and low back pain treatment in a spa therapy resort [30]. Individual randomization suggests recruitment difficulties (incomplete intervention group risk) and feasibility, as well as an increase in the number of patients lost to follow-up in the control group.

The randomisation list will be established by the methodologist in charge of the project before starting the trial. Population groups will be assigned to arms by stratified randomization by center: this randomization allows for controlling eligibility and for communicating some information relative to randomisation from the investigator and eventually other actors. A document detailing the procedures for randomisation is kept confidential. Participants will be allocated to one of two arms (Figs. 1 and 2).

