### Self-management exercise program

The main objective of the self-management exercise program will be to allow people to understand the importance of physical exercise practice and learn when, where and how to practice exercise, in order to adapt their PA practice according to their phenotype and integrate it long term in their daily life.

Each session will consist of 45 min of self-management education and 45 min of PA practice, with aerobic training program, strength training, range of motion and personal feedback. The exercise program will be tailored to each participant. The physiotherapist or adapted PA instructor will drive an experimental arm of 5 to 7 participants. The 5 sessions will take place on days (D) D4, D7, D10, D13 and D16.

For each workshop, a specific objective and operational objectives are defined, linked to criteria and indicators (Table 1).

**Table 1 Tab1:** Self-management education program

Session	Objectives
Session 1: ᅟEvaluate the representation of the patient’s PA	- Identify the representation of PA
	- Identify the barriers to and facilitators of regular PA practice
	-Acquisition of knowledge about OA
	-Know the methods of the exercise practice
Session 2: ᅟDefining the importance of exercise in knee OA	-Name the benefits of PA in the management of knee OA
	-Identify the normal and abnormal physiological signs during the PA practice
	- Learn to adapt the exercise according to its knee OA (intensity, duration)
Session 3: ᅟPatient engagement in regular PA practice	- Determine where, when and how to exercise throughout the year
	- Include an exercise program in everyday life
	- Know the anatomical bases necessary for performing the adapted exercises
Session 4: ᅟThe consequences of stopping the exercise program	-Know the importance of maintaining exercise program on a regular and long-term basis
	-Identify factors that could facilitate or limit the continuation of the exercise program
	-Learn how to build a PA session
Session 5: ᅟKnowledge restitution	- Know the means of managing knee OA
	- Know how to live healthy with knee OA
	-Set an achievable goal

*PA* physical activity, *OA* osteoarthritis

To facilitate the workshops, different teaching tools and techniques will be used: paper board, thematic discussion, participative discussion, practical leaflets (Borg scale, deconditioning circle), information booklet, exercise demonstration, feedback, and pain coping skills.

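### Two allocation rules are given that do not match; under monthly alternation those who consent and screen can foresee the arm, which can inflate the false-positive rate

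*Protocol article*

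**What the plan says.** The Abstract describes a "quasi-randomized controlled trial with an alternate-month design (1-month periods"), and Study design and setting repeats it: "The population will be randomised according to the alternate-month design method in 2 arms: experimental and active comparator". The trial is planned over two years: "This is a 2-year multicenter, prospective, comparative, and quasi-randomized trial".

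The Randomisation section also has the methodologist draw up a list before the start, and says: "Population groups will be assigned to arms by stratified randomization by center". It then says that "this randomization allows for controlling eligibility and for communicating some information relative to randomisation from the investigator and eventually other actors", and in the next sentence that the document describing the procedure is confidential.

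Under Participants and recruitment, "the research coordinator will perform the information and consent process and the physician will verify the inclusion criteria". Patients are approached by letter because they are already registered for spa therapy, and by posters. A high IPAQ class is an exclusion criterion. The primary outcome is the proportion changing by at least one class on the same self-administered questionnaire at 3 months. It is tested by chi-squared or Fisher's exact test, followed by a logistic mixed model with centre as a random effect.

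The Discussion names quasi-randomisation as a possible limitation and defends it on contamination. The Randomisation section adds recruitment difficulty and loss to follow-up in the control group. Neither mentions selection at consent or screening.

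**The concern.** A fixed alternation leaves at most the starting arm to be randomised; a randomisation list implies that later months are random too. A reader cannot tell which rule will be run, and the choice decides whether allocation can be concealed at all.

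If months strictly alternate, everyone enrolled in a centre-month gets the same arm and the sequence is public once one month has been seen. Keeping the procedure document confidential cannot hide a rule that the article itself publishes. Those who explain the study and judge eligibility can then act, even without intent, in the light of the coming arm. Patients may also decide differently if they learn that the month includes five extra sessions of 1.5 h.

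The stake is the primary endpoint. A patient classed as low can move up two classes, one classed as moderate can move up one, and one classed as high is not enrolled. Differences between months in who enters, or in how motivated they are, feed straight into the proportion that moves up, and the primary test does not adjust for them.

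**Working it through.** **1. The passages side by side**

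| Question | What the article gives |
|---|---|
| How is the arm set? | Alternate months of one month each; also a centre-stratified list |
| Who can foresee it under alternation? | Anyone who has seen one month's arm at that centre |
| Who is said to be unaware? | Only the spa therapist, as to which patients are in the trial (SPA therapy treatment) |
| Who decides entry? | Research coordinator (consent) and physician (criteria) |
| Is entry fixed before the arm can be foreseen? | No such step in the text shown |

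**2. The plan's own figure**

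Inputs from Sample size estimation: 25% vs 5%, two-sided 5%, 80% power, 65 per group. The pooled formula, with mean rate 0.15, is

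n = [1.96·√(2·0.15·0.85) + z·√(0.25·0.75 + 0.05·0.95)]² / 0.20²

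This gives 49 per group at 80% power (z = 0.842) and 65 at 90% (z = 1.282). So 65 does not match the stated 80%. That is a separate matter, errs on the safe side and does not affect this point. I use 65 per arm below.

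**3. How small a difference is significant**

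Take 3/65 (4.6%) against 10/65 (15.4%), a difference of 10.8 points. The pooled rate is 13/130 = 0.10, the standard error is √(0.10·0.90·2/65) = 0.0526, and z = 0.1077/0.0526 = 2.05. That is significant at about half the 20-point target. One patient is 1/65 = 1.5 points.

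**4. Possible size of a selection difference (all inputs assumed)**

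- Motivation: 10% of experimental-month recruits join only because exercise is offered and would move up at 50% regardless, instead of 5%. Then 0.10 × (0.50 − 0.05) = 4.5 points.
- Case mix: the share of low-class patients differs between arms by 10 to 30 points, and low-class patients move up more often than moderate-class patients. The lowest case is 0.10 × (0.20 − 0.05) = 1.5 points; the highest is 0.30 × (0.40 − 0.10) = 9 points.

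**5. Effect on the false-positive rate**

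Exact enumeration of the uncorrected chi-squared test, 65 per arm, control rate 5%, no treatment effect:

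| Difference due only to selection | Trials significant at two-sided 5% |
|---|---|
| 0 points | 4.7% |
| 4.5 points | about 16% |
| 5 points | 19% |
| 10 points | 49% |
| 15 points | 77% |
| 20 points | 92% |

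**6. Season**

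With strict alternation over 12 equally filled months, a smooth annual cycle cancels between arms (0.00 of its amplitude). With assumed opening seasons of 7 to 9 months, the worst imbalance is 0.22 to 0.23 of the amplitude. For an assumed amplitude of 10 points that is 0.23 × 10 ≈ 2 points. Because 12 is even, strict alternation would put each calendar month at a centre in the same arm in both years, so such an imbalance would not average out at that centre.

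**The case against.** The design is openly labelled quasi-randomised, conceded as a limitation, and argued for on contamination, recruitment and follow-up. Most patients are already booked for spa therapy, so they can hardly be steered to another month. The methodologist makes the list and the procedure is confidential. A supporting model adjusts for centre and covariates. Figs. 1 and 2, not shown here, may give the order of steps, and the article condenses a fuller protocol. All of this stands. None of it removes predictability under alternation, though: prior booking limits the choice of month, not who consents or is judged eligible.

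Four stronger readings are tempting and not supported:

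- **That staff are told the arm.** The sentence on communicating information is garbled, its direction is unclear, and a statement of confidentiality follows it. The point rests on predictability alone.
- **That the same staff consent, screen and take the baseline IPAQ.** The article names two roles, and the IPAQ is self-administered.
- **That selection could create the whole 20-point target difference.** The assumed inputs give 1.5 to 9 points. That raises the false-positive rate but does not readily reach 20.
- **That season is a main driver.** Alternation puts both arms in every season, and the residual is about 2 points under assumed inputs. If centres start in opposite arms, which stratification by centre would permit, it offsets further.

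**Conclusion.** The point holds in this form: the Randomisation section gives two allocation rules that must be reconciled, and the alternating one is predictable by those who obtain consent and verify eligibility, with no step in the text shown that closes entry first. Since baseline IPAQ governs both entry and room to improve, and the primary test is unadjusted, differential consent or eligibility can lift the false-positive rate from 4.7% to about 16% at 4.5 points, or about 49% at 10 points.

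These rates rest on 65 per arm, a 5% control rate, the uncorrected chi-squared test and no treatment effect. The size of the selection difference is assumed throughout. Its direction is assumed too; selection the other way would hide a benefit. Season is a minor secondary point. This is a worthwhile, inexpensive improvement to a disclosed design, and does not show that the result will be biased.

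**What to change.** - **State one rule** in Randomisation, Study design and setting and the Abstract, and say who knows each month's arm and from when.
- **Keep whole months as the unit**, but randomise the order of arms separately per centre, in blocks of varying length, with the list held by the methodologist. Fixed two-month pairs would leave every second month predictable.
- **Delay disclosure.** Complete consent, the eligibility check and the self-completed baseline IPAQ before the month's arm is disclosed. The programme timetable leaves room: "The 5 sessions will take place on days (D) D4, D7, D10, D13 and D16". This step carries most of the protection, because no ordering of months is wholly unpredictable.
- **Use one neutral information sheet and consent form** in all months.
- **Report screened, eligible and consented counts by centre-month**, so that differential entry can be seen.

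If alternation is already running, apply delayed disclosure and the counts to the remaining months; where a second year remains, reverse its order. If enrolment has ended, the counts can still be reported as far as they were recorded. I would not add a season term: the residual is small, and sine and cosine terms would use two parameters where about 65 × (0.25 + 0.05) ≈ 20 events are expected.

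The cost is an amendment to the list and to the order of enrolment steps. The downside is that same-arm months can fall in succession and centres learn the arm a few days later. Protection against contamination stays, because patients in the same centre-month still share one arm.

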**Fig. 1 Fig1:**
[figure not shown]
Flow of the participants through the study

**Fig. 2 Fig2:**
[figure not shown]
Study design

### Interventions

Both groups will receive 18 sessions of STT over 3 weeks and an education booklet on the benefits of PA practice illustrated with pictures and a detailed description of the exercises to perform (Additional file 1). Only the experimental group will receive the self-management exercise program. The aim is to propose a reinforcement of the STT effect through a self-management exercise program.

The STT and the self-management exercise program will be standardised and designed by expert spa therapy physicians.

Interventions have been designed by a specialist steering committee, standardized and reproducible for the 3 centers. The steering committee consists of investigators, a spa therapist, physician and physiotherapist and the university hospital’s medical team (physician, physiotherapist, adapted PA instructor).

Meetings with all members of the steering committee are organized to obtain consensus on the therapeutic protocol describing precisely the content and the organization of the intervention taking into account the context and the expertise of the different centers involved in the study.

